### Measures of BG

For the control group, BG data will be scanned at each clinic visit, with identifying labels removed, and stored in an anonymised file with each participant allocated a unique code. BG readings will then be transcribed from the paper charts, with BG results stored on a secure anonymised database. These data will be verified with readings downloaded from the patient's glucose meter at the end of the pregnancy using the same unique ID for later comparison. The intervention group data will be extracted from the website and stored on a secure anonymised database using a unique ID.

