### Standard clinic care group

Participants in the standard clinic care group will self-record their BG values in a paper diary at home. They will be scheduled to attend the maternity diabetes clinic every 2–4 weeks where a midwife or specialist will review their readings. If, between visits, they have two or more consecutive postprandial readings ≥7.8 mmol/L or fasting readings ≥5.9 mmol/L or one reading above 9.0 mmol/L at any time of day, they will be instructed to leave a phone message for the specialist diabetes midwife. The midwife will return their call and provide further discussion and dietary advice within 72 h. If pharmacological treatment is required, the participants will be referred to the consultant-led diabetic clinic to start treatment.

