### Description of the GDm-health system

The development of the GDm-health system has been described previously.^8^

Each connection between the front-end (smartphone application) and the back-end (server and web interface) will be securely established on an encrypted channel and—for privacy reasons—the front-end will not contain any person-identifiable information (ie, participants will be identified by numeric ID). In order to avoid errors while reporting the BG measurement, the glucometer to be employed (LifeScan OneTouch UltraEasy) will be connected to the smartphone via a third-party Bluetooth module (Polytel Wireless GMA—Polymap). The LifeScan OneTouch UltraEasy is the glucometer of choice as it is compliant with the ISO 15197:2003 standard for blood glucose monitoring systems for self-testing in managing diabetes mellitus (this ISO standard was applicable at the time of the RCT). Readings will be transferred automatically to the Android application running on the smartphone at the time of the BG measurement, with no need of manual input.

As soon as the BG reading is stored in the smartphone's memory, the participant will be asked to ‘tag’ the reading as preprandial or postprandial through the smartphone application interface. Through the application, she will also be able to enter additional free-text comments as well as dosage and type of medication taken around the time of each reading.

All information will be transmitted to the back-end server automatically when the participant exits the application or as soon as the smartphone connects to the mobile network. The BG readings and associated information entered by the participant will be displayed together on the web interface for the benefit of the clinician reviewing the data.

Data review will be possible in two different ways: a table of all the readings taken by the patient listed in reverse chronological order and a graphical display of the readings to highlight the difference between preprandial and postprandial BG levels (values will be displayed as green, yellow or amber according to the corresponding alerting thresholds).

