### Safety

Supervision in the form of weekly meetings with the clinicians, research team and the diabetes midwives will occur to ensure adherence to the protocol and to resolve problems and queries.

The use of self-capillary BG monitoring is well established in the pregnant and non-pregnant population. Safety concerns include adequate alerts if the remote glucose testing groups have either high or low BG readings or are not providing readings. This will be addressed by having automatic alerts activated to ensure abnormal results are not ‘missed’. The equipment to be used is a standardised, approved glucose meter with Bluetooth technology. It has been used in numerous previous studies and found to be robust. Decisions about patient care will continue to be made by trained doctors and midwives. The technology will not be relied on to automatically alert patients or provide automatic changes in management in response to the readings the system receives.

The m-health system uses a standard BG meter (OneTouch UltraEasy, LifeScan, Inc), which connects to a smartphone (HTC Desire C with Android Operating System V.4.1) via a commercially available Bluetooth adapter (Polytel Wireless Glucose Meter Accessory (GMA), Polymap Wireless LLC). The users measure their BG in the same way as usual care, but the GDm-health system allows a copy of the readings to be transmitted to the smartphone via Bluetooth. The readings are then transmitted to a secure NHS server in real time via the mobile phone data network, using checksums and encryption to ensure data integrity. The BG readings are stored in the user's meter, as well as in the smartphone memory and on the NHS server. No patient-identifiable data are transmitted between the meter and the phone or between the phone and the NHS server.

A business continuity plan has been developed to ensure women using the GDm-health system and their healthcare professionals have a contingency plan if the system fails.

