### Ethical issues

The same treatment algorithms will be used between the two groups; therefore, the clinical care received will strive to be similar, although the method of delivery of that care will differ. To ensure hardware and patient satisfaction questionnaires are returned, each participant will receive a £20 shopping voucher once they have sent back their meters, phones and questionnaires.

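### Control-arm glucose values enter the database from hand-written diaries while intervention values upload automatically; device-recorded readings should be named as the primary source in both arms

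*Protocol article*

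**What the plan says.** **Control arm.** Under Standard clinic care group: "Participants in the standard clinic care group will self-record their BG values in a paper diary at home". Under Measures of BG, "BG data will be scanned at each clinic visit", and then "BG readings will then be transcribed from the paper charts, with BG results stored on a secure anonymised database". The next sentence adds a check: "These data will be verified with readings downloaded from the patient's glucose meter at the end of the pregnancy". The stated purpose of that download is a later comparison.

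**Intervention arm.** Under Description of the GDm-health system: "Readings will be transferred automatically to the Android application running on the smartphone at the time of the BG measurement", with no manual entry. That section gives the avoidance of reporting errors as the reason for linking meter and phone. Under Measures of BG: "The intervention group data will be extracted from the website and stored on a secure anonymised database using a unique ID". No meter download is described for this arm.

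**Common to both arms.** The Randomisation section specifies the same meter model for all women. The Safety section says that, in the m-health system, readings are kept in the meter "as well as in the smartphone memory and on the NHS server". Under Ethical issues, participants receive a voucher "once they have sent back their meters, phones and questionnaires".

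**Outcome and design.** The trial is open-label. The primary outcome is mean blood glucose from recruitment to delivery, adjusted for the number of readings, the preprandial/postprandial mix and time in study.

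**The concern.** The two arms reach the analysis database by different routes. A control value gets there only if the woman writes it down, writes it correctly, and someone transcribes it. An intervention value gets there without any of these steps. Reporting error is engineered out of one arm and left in the other.

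Control women also know that certain high readings oblige them to telephone the midwife and may lead to referral for treatment, so a motive for selective recording is conceivable.

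The other safeguards do not reach this problem:

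- Intention-to-treat analysis and analysts blinded to allocation act after the values have been recorded.
- Adjusting for the number of readings and the meal mix cannot correct an altered value or recover a selectively omitted one. The number of readings is itself recorded differently by arm.

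The primary outcome is exposed. So are the percentage of readings on target and the compliance summary, which would set diary entries against uploads.

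**Working it through.** **1. The plan's own figure.** Inputs from Sample size: SD 0.8 mmol/L, 100 women per arm, power 80%, significance level 0.05 (taken as two-sided).

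- Standard error of the contrast: 0.8 × √(2/100) = 0.113 mmol/L.
- Detectable difference: 0.113 × (1.960 + 0.842) = 0.317 mmol/L. The stated 0.32 reproduces.
- Power at 0.32: 80.7%. The number needed is 99 per arm.

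The sample size is not in dispute.

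**2. Size of a possible recording bias.** The documents give no diary error rate and no direction, so everything in this step is an assumption. Suppose individual readings follow N(6.2, 1.3²) mmol/L, and a fraction q of control readings at or above 7.8 (the postprandial action threshold in the treatment-allocation sections) is left out at random.

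- Share of high readings: p = P(Z ≥ (7.8 − 6.2)/1.3) = P(Z ≥ 1.231) = 0.109.
- Mean of the high readings: 8.43, which is 2.23 above the overall mean.
- Fall in the recorded control mean: b = q × p × 2.23 / (1 − q × p).

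In the table, power is for a true benefit of 0.32, that is Φ((0.32 − b)/0.113 − 1.96). The false-positive rate is two-sided with no true effect.

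| q | b (mmol/L) | b / 0.32 | Power | False-positive rate |
|---|---|---|---|---|
| 0 | 0 | 0% | 81% | 5.0% |
| 10% | 0.025 | 8% | 74% | 5.5% |
| 20% | 0.050 | 16% | 67% | 7.2% |
| 30% | 0.075 | 24% | 58% | 10.2% |
| 50% | 0.129 | 40% | 39% | 20.6% |

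Other assumed error patterns give similar sizes:

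- 10% of control readings written 1.0 mmol/L too low: b = 0.10 × 1.0 = 0.10.
- 5% of readings omitted that lie 2.0 above the mean: b = 0.05 × 2.0 / 0.95 = 0.105.

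At b = 0.10, power is 49% and the false-positive rate 14.3%.

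**3. Readings after the last scanned visit.** Control visits are every 2–4 weeks. On average, half an interval, 1–2 weeks, would fall between the last scan and delivery. If those readings were lost and glucose drifted linearly by an assumed 0.02–0.05 mmol/L per week, a simple mean would shift by slope × weeks / 2, which is 0.01 to 0.05 mmol/L. The planned mixed model over gestational age would absorb most of a linear drift, so this part is not added to the table.

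**The case against.** The strongest reply is that the plan already brings in objective data for the control arm. The sentence after the transcription step provides for checking against the meter, and checking can include correcting. The end-of-pregnancy download also offers a route to readings after the last visit, and the Sample size section says that all data from recruitment to delivery will be used. On that view, all that is missing is a rule on which source prevails, a detail that a journal article commonly leaves to the full protocol or analysis plan.

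Much of this stands. A reader might infer three stronger things that the documents do not support:

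- **That meter data are excluded from the analysis.** The text does not say so. It says only that they verify the diary data and serve a later comparison.
- **That control readings after the last visit are lost.** They may be recovered from the download; their use is simply not stated.
- **That a true effect could be reversed.** Even with half of all high readings omitted (0.129) and the largest drift figure (0.05), the sum of 0.179 leaves 0.32 − 0.179 = 0.141 mmol/L of the planned effect in the same direction. The shifts at 10–30% omission are all smaller than one standard error.

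The direction is also open. Under-recorded highs would flatter control, but other errors could act the other way. An intervention woman who stops using the phone drops out of the website data too, although the low-reading alert to the midwife limits that gap.

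The argument that this is only omitted detail does not stand. The article does state a source for each arm, and the sources differ: diary in one, device in the other. That is a choice about how the primary outcome is measured, and a better one is available with equipment already in use.

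**Conclusion.** The concern holds as a risk of differential recording error, not as a demonstrated bias. As written, the diary supplies the control values and the meter checks them, while the device supplies the intervention values. No sentence carries meter values into the control data where the two disagree.

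The size is unknown. Under the assumed distribution and 10–50% omission of high readings, it is about 0.025–0.13 mmol/L against a target of 0.32, enough to lower power from 81% to between 74% and 39%. These rates are illustrative only. If verification in practice means that meter values correct and complete the diary data, most of the recording effect on the values disappears, and the text should say so. The full protocol or analysis plan, not seen here, may already do this.

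**What to change.** State before analysis that device-recorded readings are the primary source in both arms:

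- **Control:** the time-stamped meter download already planned at the end of pregnancy.
- **Intervention:** the automatic upload, supplemented by the returned meter's memory where uploads are missing.
- **Diary and app:** used only to tag readings as preprandial or postprandial.
- **Fallback:** diary data (control) or website data (intervention) where a meter is lost or its memory does not cover the whole period, with the number of women affected reported by arm.
- **Reporting:** diary–meter agreement in the control arm (omitted, altered and extra entries), and a sensitivity analysis using the diary-based control data.

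Apply the same source to the on-target percentages and the compliance summary.

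The cost is small: a few sentences of text, and downloads from intervention meters that are returned anyway. The sample size does not change. The drawback is that only the app is described as tagging readings, so some control readings will need a meal tag inferred from the time stamp or the diary. Downloads at each visit are not essential. If they are added to guard against limited meter memory, the download should not be shown to clinicians in the standard-care arm, since their review there rests on the self-recorded diary and seeing the download could change the comparator.

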### Accrual and analysis

#### Sample size

The four published randomised trials that investigated the effect of a telehealth intervention on mean BG control in pregnancy reported SDs between 0.2 and 1.2 mmol/L. The lower value was from a very small study (n=19) conducted in 1996.^22^ The range of SD for mean BG in the three relatively large studies (n>30) was 0.5–1.2 mmol/L.^13^
^15^
^17^ This indicates that we do not yet have a precise estimate of the likely SD in mean BG, making sample size calculation challenging. We therefore pragmatically decided to assume an SD of 0.8 mmol/L for the mean BG level at the end point. Thus, with 100 patients in each arm, we will be able to detect a difference between the arms of 0.32 mmol/L, with power of 80% and a significance level of 0.05.

The multilevel analysis we propose has not been conducted in any of the previous studies and will use all the data from recruitment to delivery. Thus, the difference in BG between the arms at the study end point will be estimated more precisely compared with a trial that uses a comparison of mean BG at the end point alone or a mean of all readings. Therefore, the calculation given provides a conservative estimate of the effect size that could be detected.

### Statistical analysis

#### Descriptive analyses

Baseline demographic characteristics of each group will be tabulated. The number of patients, number of missing values, the mean, range and SD of continuous variables, and the frequency of the binary variables will be reported.

The analyses will be based on the intention-to-treat (ITT) population, which will include all patients randomised. A per-protocol analysis will also be performed excluding women who did not use the GDm-health system for at least 67% of expected BG readings (at least 18 readings per week) to determine the efficacy of the system under optimal use. This level was selected as it was programmed at the beginning of the trial as the level at which the computerised system would alert healthcare professionals that a woman was non-compliant with system use.

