**Figure 3 BMJOPEN2015009702F3:**
[figure not shown]
Study overview.

BG monitoring targets, dietary advice and thresholds for starting medication will be the same for both allocation groups. All women will be asked to test their BG six times a day on at least 3 days of the week, as per the local guideline. This consists of a fasting sample, 1 h post breakfast, pre-lunch, 1 h post lunch, pre-dinner and 1 h post dinner. Optimal BG is a fasting reading ≥3.5 and ≤5.8 mmol/L and 1 h postprandial readings below 7.8 mmol/L.^11^ If there are persistently high BG readings, or medication is deemed to be required, women will be asked to increase monitoring to 7 days/week.

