**Figure 4 BMJOPEN2015009702F4:**
[figure not shown]
The GDm-health Management System.

Participants will be invited to contact the specialist diabetic midwife using a call-back request function in the smartphone application, or by phone call, if they have any concerns. A specialist diabetes midwife will review the results of the remote monitoring at least three times a week. If a participant has two or more consecutive postprandial readings ≥7.8 mmol/L or fasting readings ≥5.9 mmol/L or one reading above 9.0 mmol/L at any time of day, the specialist midwife will call the participant or send an SMS message from the web interface to the participant’'s phone inviting discussion and further dietary advice. If fewer than 12 of the minimum 18 readings a week are being done, an automatic alert will be generated on the web interface for the diabetes specialist midwife. If this alert persists for 2 weeks, the specialist diabetes midwife will contact the participant. If there is evidence that pharmacological treatment is required, the participant will be referred to the consultant-led clinic to start treatment. Further dose adjustments and messages of advice/encouragement will be communicated to the participant between clinic visits via the GDm-health management system by the specialist diabetes midwife.

Measures taken in both groups at subsequent visits and after delivery are listed in box 1.

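### The supplementary per-protocol rule can exclude women from the intervention arm only, so its result is open to selection bias of uncertain direction, and its bracketed reading count needs clearer wording

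*Protocol article*

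**What the plan says.** Under Statistical analysis, Descriptive analyses, the protocol article sets the main population: "The analyses will be based on the intention-to-treat (ITT) population, which will include all patients randomised". It then adds a per-protocol analysis "excluding women who did not use the GDm-health system for at least 67% of expected BG readings (at least 18 readings per week", closing the bracket there, with the aim "to determine the efficacy of the system under optimal use". The 67% level is justified as "the level at which the computerised system would alert healthcare professionals that a woman was non-compliant with system use".

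Three other places bear on this rule.

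- **Remote glucose monitoring group** gives the alert: "If fewer than 12 of the minimum 18 readings a week are being done, an automatic alert will be generated on the web interface".
- **Treatment allocation** gives the schedule for both arms: "All women will be asked to test their BG six times a day on at least 3 days of the week". If readings stay high or medication is needed, "women will be asked to increase monitoring to 7 days/week".
- **Standard clinic care group** and **Measures of BG** say that controls keep a paper diary, that their charts are transcribed, and that the values are checked against a meter download at the end of pregnancy.

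No adherence criterion is stated for the control arm.

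**The concern.** The exclusion is defined by use of a device that one arm does not have. An intervention woman who tests rarely is removed, while a control woman who tests just as rarely is kept. Randomisation made the two full arms comparable. It does not make the compliant part of one arm comparable with the whole of the other. If frequency of testing is related to glucose level for reasons unconnected with the system, the per-protocol difference contains that relation as well as any effect.

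This matters because the result is presented as a statement about efficacy when the system is used well, which is a causal claim. A reader who finds a null or small intention-to-treat effect beside a larger per-protocol effect may conclude that the system works for those who use it.

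A second, smaller matter is the bracketed figure of 18 readings a week. It does not say outright whether 18 is the expected number or the cut-off, or which expected number applies to women asked to test every day.

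**Working it through.** **1. The plan's own figures.**
- Minimum schedule: 6 readings × 3 days = 18 a week (Treatment allocation).
- Alert level: 12/18 = 66.7%, which rounds to 67% (Remote glucose monitoring group).
- Per-protocol level with 18 as the expected number: 0.67 × 18 = 12.06, so 12 apart from rounding. This agrees with the alert, as the article says it should.
- Detectable difference (Sample size; two-sided test assumed): (1.960 + 0.842) × 0.8 × √(2/100) = 0.317, which reproduces the stated 0.32 mmol/L.

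**2. Other readings of the bracket.**
- If 18 were the cut-off itself, it would be 18/18 = 100% of the minimum schedule. For 18 to be 67%, the expected number would have to be 18/0.67 = 26.9 a week, a figure found nowhere in the article.
- For women asked to test daily, the schedule is 6 × 7 = 42 a week. If 42 were the denominator, the cut-off would be 0.67 × 42 = 28.1. Against 42, a count of 12 is 29% and a count of 18 is 43%. A woman giving 20 readings a week would pass a cut-off of 12 or 18 and fail one of 28.

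**3. Size of the bias from excluding in one arm only.** Suppose the system has no effect, and the least compliant fraction f of intervention women is dropped. Let r be the correlation between poor use and higher mean glucose, and let both be normally distributed. Then

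spurious difference = −r × SD × φ(z_f) / (1 − f),

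where z_f is the f quantile of the standard normal distribution and φ its density. The SD of 0.8 is the article's; f and r are assumptions. Two examples:
- f = 0.1, r = 0.1: 0.1 × 0.8 × 0.1755/0.9 = 0.016
- f = 0.3, r = 0.3: 0.3 × 0.8 × 0.3477/0.7 = 0.119

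Spurious difference in favour of the system (mmol/L):

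| Dropped | r = 0 | r = 0.1 | r = 0.2 | r = 0.3 |
|---|---|---|---|---|
| 10% | 0 | 0.016 | 0.031 | 0.047 |
| 20% | 0 | 0.028 | 0.056 | 0.084 |
| 30% | 0 | 0.040 | 0.079 | 0.119 |

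As a share of 0.32, the non-zero entries run from 0.016/0.32 = 5% to 0.119/0.32 = 37%. In a simple comparison of two means with 100(1 − f) against 100 women, the type I error rises from 5% to between about 5.2% and 16%. If r is negative, the same sizes apply against the system.

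**The case against.** The strongest reply is that this analysis is an addition. The intention-to-treat population is the basis of the analyses, and the per-protocol result is openly labelled as describing best use. That stands, and it limits the consequence. It does not repair the rule, which the article states explicitly and does not leave to a later document.

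A reader might infer more than the article supports in four ways.

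- **That the threshold contradicts the alert, 18 against 12.** It does not. The bracket directly follows the reference to expected readings, and 18 is exactly the minimum expected number. The next sentence equates the level with the alert, and 67% of 18 is 12. Taking 18 as the cut-off would make the sentence contradict itself. A woman at exactly 12 of 18 fails 67% only because 66.7% was rounded.
- **That the worst-controlled women face a cut-off of 28 and are selectively removed.** This needs 42 as the denominator, whereas both the bracket and the alert refer to 18. With 18, women asked to test daily pass more easily.
- **That the bias must favour the system.** The article gives no relation between compliance and glucose level and no expected excluded fraction. If women with high readings test more and are measured against 18, they are more readily kept, which could push the result against the system.
- **That every control would be excluded.** This is a literal reading of a sentence plainly written about intervention women.

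The usual remedies can also be criticised, and fairly. A common rule for both arms still selects on behaviour after randomisation, which the low-count alert influences in one arm only. A complier average causal effect assumes no benefit below the cut-off, which is doubtful for a woman sending 10 readings a week.

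**Conclusion.** The point holds in a limited form. Followed as written, the per-protocol rule removes women from one arm only, and the comparison cannot support its stated aim. It is open to selection bias of uncertain direction, plausibly towards the system if poor users have worse control. The illustrated size, about 0.02 to 0.12 mmol/L, rests on the article's SD of 0.8 and on assumed values of 0.1 to 0.3 for the correlation and 10% to 30% for the fraction dropped. None of the assumed values comes from the article. The bracketed 18 is an ambiguity to clear up: the natural reading is consistent with the alert, but the denominator for women testing daily is not spelled out. The primary intention-to-treat conclusion is not affected.

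**What to change.** 1. Reword the rule as at least 12 of the minimum 18 readings a week, averaged over the woman's participation, with 18 as the denominator for all women. This defines an analysis set only and changes nothing in the monitoring schedule.
2. For efficacy when the system is used well, estimate a complier average causal effect with allocation as the instrument, keeping all randomised women. State its assumption that use below the cut-off has no effect. State also that allocation brings a halved visit schedule, which must be assumed not to affect the women below the cut-off.
3. If a per-protocol comparison is kept, apply the same reading-count rule to both arms, using recorded readings verified from the meter. Label it supportive only, because it still conditions on behaviour after randomisation.

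The cost is some wording, one extra model and a wider interval. If, for example, 20% of intervention women fell below the cut-off, the intention-to-treat standard error of 0.8 × √(2/100) = 0.113 would become about 0.113/0.8 = 0.141 for the complier effect. For the one-arm per-protocol comparison it would be 0.8 × √(1/80 + 1/100) = 0.120.
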